**Figure 1 figure1:**
[figure not shown]
Study Flow. *: 60 grandchildren will be paired with their grandpaerents; NRI-RQV: Network of Relationships Inventory–Relationship Quality Version; IOS: Inclusion of Other in the Self scale; IMS: Investment Model Scale; FCQ: Friendship Chemistry Questionnaire.

### Participants

The aim is to recruit 60 grandparent-grandchild pairs, which will be split evenly into intervention and control conditions. The sample size is limited by the specific focus of the intervention and the availability of participants complying with the criteria, but it represents a valid sample for the statistical analyses. A convenience sample will be used in this study to recruit participants. We consider eligible pairs of grandchildren and grandparents meeting the following inclusion criteria.

Grandchildren should be willing to participate in the study and meet the following requirements:

Aged 18 to 30 years: we recruit young adults because this is a transition period to adulthood associated with changes in the level of interactions and relational closeness [13]Be regular users of Facebook: we use Facebook because this is the most common social media among Mongolian young adults [29], and we define regular users as those who check their accounts every 2 to 3 days or more oftenHave infrequent meetings with their grandparent: the proposed intervention is aimed at improving relationships between grandparents and grandchildren who do not have much opportunity to meet and talk. Therefore, we recruit grandchildren who live separately from their grandparents (not in the same apartment or building) and do not meet with their grandparents more than once a week on average

In addition, the grandchildren should have one grandparent willing to participate in the study who meets the following requirements:

Retired and aged over 60 years: according to Mongolian law, the retirement age is 55 years for women and 60 years for menBe able to independently communicate with a researcher: the selected grandparent will be requested to share their life story and give permission to researchers to post photos on Facebook. Therefore, we recruit grandparents who are competent to participate in the studyNot have any account on social media: the proposed intervention aims at sharing pictures and related stories with the grandchildren in a controlled environment, and thus assumes there is no other form of sharing in the grandparent-grandchild pairs occurring on social networks. Therefore, including grandparents who use social media will not match the study objectiveHave at least 15 available pictures about their life: during the intervention period, we will share Facebook posts 8 times (once a week). Each Facebook post will consist of at least 1 or 2 photos that illustrate a story. In addition, the stories will be about the different life span of the grandparent; therefore, we need 15 photos to illustrate different life stories of the grandparent

### Recruitment

Grandchildren will be recruited from the public universities in Ulaanbaatar, Mongolia, using online as well as paper-based recruitment surveys. As a first step, we will reach students by introducing the study and its goals at the end of their lectures. Those interested in participating in the study will then stay in the classroom to complete the recruitment survey and sign the consent form. The survey will include filtering questions, reflecting the inclusion criteria for grandchildren, and will ask participants to provide an email or phone number for a follow-up. Students who met our inclusion criteria and who have stated their willingness to invite their grandparents to join in our study will be contacted by the researchers to confirm the interest of their grandparents and organize a phone interview. The list of potential candidates will be managed electronically, with access provided only to the researchers in charge of the recruitment.

As a second step, the researchers will contact the grandparents for a phone interview to confirm their eligibility. At the end of the phone interview, a follow-up visit will be scheduled with the grandparents who met the inclusion criteria. We will recruit study participants and make visits until we have 60 pairs that meet the inclusion criteria and agree to participate.

### Processes and Intervention

#### Home Visit to Collect Photos and Stories

Researchers will make a home visit according to the scheduled appointments with the selected grandparents. At the beginning of the meeting, researchers will introduce themselves, explain the purpose of the study, and request that the grandparent read and sign the consent form. Researchers will then ask grandparents to bring pictures that illustrate their life history that they would be willing to share with their grandchildren. In order to ensure diversity in the pool of pictures to share, researchers will propose selecting pictures with the following characteristics: (1) relevant life events such as birth, marriages, work, etc; (2) pictures the grandparents like, find funny or interesting, or that they feel proud of; (3) pictures that include children as well as grandchildren; and (4) pictures that are very old and some more recent. During the visit, researchers will start a conversation regarding the photos by asking the story behind each picture. The researchers will digitize the picture (eg, taking a picture with a mobile phone) and take note of the stories told during the reminiscence session.

#### Premeasurement

Researchers will schedule a meeting with the participating grandchildren to complete the premeasurement questionnaire, which includes all instruments described in the Outcome Measures section.

#### Intervention

The intervention will be implemented over a period of 2 months among the participants of the intervention group. The sharing of pictures and stories will be done using Facebook closed groups. A closed group will be created for each grandchild with whom posts will be shared privately by one of the researchers using an account created for the sole purpose of the study. Grandchildren will be invited to their specific closed group before the start of the intervention with a welcome post explaining in detail the procedure of the picture sharing. A privacy feature of this setup is that sharing outside closed groups is not enabled, which means that grandchildren will not be able to share the original posts outside the closed group.

During the intervention, grandchildren will receive one post per week. The post will be composed by the research team using the pictures and stories collected during the reminiscence session. Each post will include a picture and the related story written as told by the grandparent to the researcher. It is important to note that the older adults will not be directly involved in the intervention process, as this intervention does not enable direct communication between grandparents and grandchildren (ie, grandchildren will not be able to interact with their grandparents through Facebook). Any potential interaction in the grandparent-grandchild pairs will occur through other mediums. Participants in the control condition will only participate in the pre- and postmeasurement sessions. All participants are informed verbally and in the informed consent of their rights, which includes leaving the study at any moment.

#### Postmeasurement

After 2 months of intervention, the grandchildren in both intervention and control groups will be invited for an individual meeting to perform postmeasurement. The same questionnaires provided in the premeasurement session will be used. In addition, the participating grandchildren will be debriefed on their experience during the intervention, and on if and how it affected their relationship with their grandparent.

### Outcome Measures

#### Primary Outcomes

The Inclusion of Other in the Self (IOS) scale and the Network of Relationships Inventory–Relationship Quality Version (NRI-RQV) will be used to measure the relationship of grandparent and grandchild.

IOS is a pictorial tool developed to measure the degree of interpersonal connectedness. In this study, a modified version of the IOS by Gächter et al [30] will be used. This instrument was chosen because it is validated and more comprehensible than the original measure. The NRI-RQV is a combination of the Network of Relationships Inventory and a family relationship measure developed by Buhrmester and Furman [31]. This 30-item survey has 10 scales with 3 items per scale. In this study, the 5 positive features—companionship, intimate disclosure, satisfaction, emotional support, and approval—of the NRI-RQV will be used as a measure of closeness between grandchildren and grandparents. The original questions were adapted by replacing the pronouns with grandparent to fit the grandparent-grandchild relationship.

#### Secondary Outcomes

We will rely on the Investment Model Scale (IMS) [32] and self-reported communication frequency to measure relationship investment. The IMS is an instrument developed to measure commitment level and 3 bases of dependence, which are satisfaction level, quality of alternatives, and investment size. The IMS includes a specific subscale on relationship investment that will be used to measure the grandchild’s contribution in this relationship. The original questions were adapted to the grandparent-grandchild relationship by replacing the word partner with grandparent. Relationship investment scales are scored by computing the scores with higher scores representing higher commitment. Communication frequency between the grandparent and grandchildren will be measured with a custom question with response values going from a few times a week to never.

We rely on the Friendship Chemistry Questionnaire (FCQ) [33] and a custom-made set of questions to measure conversational resources. The FCQ was developed to explore friendship formation factors, comprising 5 subscales: reciprocal candor, mutual interest, personableness, similarity, and physical attraction [33]. In this study, reciprocal candor and similarity scales of the FCQ will be used to estimate available conversational resources, as they reflect on the openness and predisposition toward each other. The original questions were adapted from friendship to the grandparent-grandchild relationship by replacing the pronoun. The FCQ is scored by averaging the items with high scores representing the higher levels of each scale. Two separate questions were redacted and added by researchers to assess general conversational resources and identify common conversational topics with grandparents.

As part of the debriefing interview with participants, researchers will inquire about how the intervention affected their relationship with their grandparent, including recent positive and negative episodes of interaction with grandparents and what pictures and stories captured their attention and led to more interactions. These insights will be contrasted with the online reactions and comments on the posts.

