The sharing of family memories in this context is unidirectional: family memories are used as triggers to give grandchildren topics of conversations, stimulate social interactions, and eventually increase their sense of connectedness. All social interactions with grandparents happen outside social media, either by phone or face to face, and, in principle, without the grandparents having to use technology or have a social media presence. This approach is well suited to scenarios where the practice of reminiscence is widely adopted, such as in nursing homes, where family memories can be used as a bridge to connect grandchildren with their (often frail) grandparents [24,25].

The study is inspired by the practice of reminiscence, the process of recollecting past memories—a practice that is common at all ages [26] and often conducted with older adults due to its many functions and benefits. Webster [27] identifies 8 particular functions: death preparation, identity, problem solving, teach and inform, conversation, boredom reduction, bitterness revival, and intimacy maintenance. Thus, reminiscence serves an important social function in facilitating the sharing of personal memories with others, helping to create bonds between people [28], offering an interesting platform for grandchildren to learn about their grandparents and build family history [5], potentially reconnecting with their grandparents.

In this protocol, we focus on studying the effects of sharing grandparents’ pictures and related stories with grandchildren on social media. Thus, the sharing is mediated by technology. In doing so, we address the following main research question:

RQ1: Does sharing old pictures and related short stories (from grandparents) with young relatives increase their relational quality?

With this research question, we study the impact of the intervention on the intergenerational relational quality from the perspective of the grandchildren, measured as the feeling of closeness with their grandparents. In addition, we look at two main factors contributing to relational quality and observe if these factors increase as a result of the intervention. More precisely, we address the following secondary research question:

RQ2: Does sharing old pictures (from grandparents) with the young relatives increase their relational investment?

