We particularly focus on relational investment as captured by the impact on the grandchildren’s commitment in their relationship with their grandparents, as well as on the frequency of communication.

RQ3: Does sharing old pictures (from grandparents) with the young relatives provide them with more topics of conversations and relationship chemistry?

We focus on conversational resources as captured by the impact on the openness and predisposition toward each other (relationship chemistry), as well as on the number and diversity of topics of conversation.

The potential impact of the study is to validate an approach to improving relationship quality between grandparents and grandchildren by empowering grandchildren through the sharing of family stories. This approach can complement existing online and colocated reminiscence technology that generally assume active collaboration of family members to keep the older relatives socially active.

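### The communication-frequency item for RQ2 has no answer above a few times a week and eligibility does not limit phone contact, so pairs that start in the top category cannot show an increase on this one secondary measure

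*Protocol article*

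**What the plan says.** RQ2 asks about a rise: "Does sharing old pictures (from grandparents) with the young relatives increase their relational investment". The Objectives section says this is captured by the grandchild's commitment "as well as on the frequency of communication". Secondary Outcomes names the two instruments: "We will rely on the Investment Model Scale (IMS) [32] and self-reported communication frequency to measure relationship investment". The frequency item was written by the team and is "measured with a custom question with response values going from a few times a week to never". Under Postmeasurement, the premeasurement questionnaires are given again, so the same upper limit applies on both occasions.

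The Participants section describes the target as grandchildren and grandparents "who do not have much opportunity to meet and talk". The criteria that put this into practice are that the two live separately and "do not meet with their grandparents more than once a week on average". No criterion concerns calls. The Objectives section states the channels of contact: "All social interactions with grandparents happen outside social media, either by phone or face to face".

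On size, "The aim is to recruit 60 grandparent-grandchild pairs, which will be split evenly into intervention and control conditions". The Statistical Analysis section plans, for RQ2, an ANOVA with group and time as factors and the interaction between them.

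**The concern.** The outcome is meant to detect more contact, but its scale stops at a level that an eligible pair can already have reached. Living apart and meeting at most weekly does not prevent a grandchild from phoning several times a week. Such a grandchild gives the highest answer before the first post. If calls then become daily, the recorded change is zero. For that pair, one additional contact a week, a plausible response to one post a week, also leaves the answer unchanged.

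What is at stake is the sensitivity of the only direct measure of how often the pair communicate. The Investment Model Scale covers commitment and investment, not contact. If the intervention raises contact, the cap reduces the observed difference between arms on this item, and a null there could be over-read as evidence that communication did not change.

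**Working it through.** **Step 1: does the ceiling exist?** Four statements, taken together:
- Secondary Outcomes gives both end points of the item, and nothing lies above *a few times a week*.
- Participants restricts housing and meetings only.
- Objectives counts phone contact as interaction and asks about an increase.
- Postmeasurement repeats the same questionnaire.

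It follows that a pair in the top category at premeasurement can stay there or fall, but cannot rise. This needs no assumption beyond the stated end points. Wording the top option as that frequency or more would not change it.

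**Step 2: is there a figure in the plan to reproduce?** No. The article gives no power, effect size or standard deviation for this item, and no share of pairs by category. The rest is therefore illustrative.

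**Step 3: simulation on assumed inputs.**
- From the article: 60 pairs split evenly, so 30 per arm; one measurement before and one after.
- Assumed: each pair's underlying frequency is normal with SD 1 category; each occasion adds noise with SD 0.5; the intervention shifts the post value by 0.6 category. Answers are rounded and capped at 5 categories or, for comparison, at 7. The mean is varied to change the share at the top.
- Test: two-sided t test at 0.05 on the change scores. With two time points this is the group-by-time interaction.

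| Share at the top of the 5-category item at baseline | Difference in change, cap 5 | Difference in change, cap 7 | Power, cap 5 | Power, cap 7 |
|---|---|---|---|---|
| 9% | 0.55 | 0.59 | 0.75 | 0.80 |
| 33% | 0.44 | 0.59 | 0.65 | 0.80 |
| 50% | 0.35 | 0.59 | 0.53 | 0.79 |

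The observed difference shrinks by 1 − 0.55/0.59 = 7%, 1 − 0.44/0.59 = 25% and 1 − 0.35/0.59 = 41%.

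**Step 4: the same loss as sample size.** By the normal approximation, the ratio of pairs needed is (1.96 + z of power without the low cap)² / (1.96 + z of power with it)².
- 9%: (1.96 + 0.84)² / (1.96 + 0.67)² = 7.85 / 6.94 = 1.1
- 33%: 7.85 / (1.96 + 0.39)² = 7.85 / 5.50 = 1.4
- 50%: (1.96 + 0.81)² / (1.96 + 0.08)² = 7.65 / 4.14 = 1.8

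**Step 5: comparison with a cruder formula.** If every pair at the top contributes nothing and the SD is unchanged, the ratio is 1/(1 − p)². This gives 1/0.67² = 2.2 at 33% and 1/0.50² = 4.0 at 50%, well above Step 4. There are two reasons for the gap. The cap also narrows the spread of change scores. And some pairs at the top would have drifted down without the intervention, so a prevented fall still counts toward the difference between arms. The 7-category comparator is itself capped, so Step 4 slightly understates the loss.

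**The case against.** The strongest reply is that the harm is assumed. The article never says how many pairs start at the top, and several features suggest a low-contact sample: separate homes, infrequent meetings, and an Introduction that describes weak relational investment by young adults and grandparents who hold back from contact. If about 9% start at the top, the loss is small. This stands, and it is why no single figure can be given. Against it, the screening account under Challenges and Lessons Learned shows that grandparents had to live in Ulaanbaatar, and the grandchildren were volunteers willing to invite them. Frequent calls are therefore plausible, though not established.

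Some stronger readings are tempting but not supported:
- *RQ2 cannot be answered.* A reader might infer this, but the Investment Model Scale is untouched by the cap and can show an increase in the other part of RQ2.
- *A null could not be told apart from a ceiling.* The item is given before and after in both arms, so the share at the top is observable.
- *The trial would need 1.6 to 2.8 times the pairs.* That comes from the Step 5 formula with an assumed 20% to 40% at the top (1/0.8² = 1.56; 1/0.6² = 2.78). It holds the SD fixed and overstates the loss.
- *A weekly visitor who also phones once or twice is certainly at the top, so channels must be asked separately.* The item's wording, its number of categories and how it treats calls and visits are not printed. An article may leave these to the questionnaire.

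Stratifying on initial closeness may balance frequent callers between arms, but it does not remove the ceiling.

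**Conclusion.** The point holds for one item. The stated top category and the absence of any limit on phone contact mean that a pair starting at the top cannot record an increase. When the intervention truly raises contact, this biases the group-by-time effect on communication frequency toward zero. It does not reach the Investment Model Scale or the two primary instruments.

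The size depends on a baseline share that the article does not report. Under the assumed shift, spread and 30 pairs per arm, the loss is minor at 9% (about 1.1 times the pairs) and material at 33% (about 1.4 times). This is a limitation of a secondary measure that is easily avoided in the design and can be checked in the data.

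**What to change.** **For any further use of the protocol:** add response options above the present top, for example almost daily, daily and more than once a day, or ask for the number of contacts over a fixed recent period. Use the identical item before and after in both arms. The team wrote the question, so the cost is a slightly longer item, with no extra visit, staff or participants.

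**For the data already collected:** the article reports that collection finished in November 2019, so the item cannot be changed for this dataset. The report should then:
- give the share in the top category at premeasurement by arm;
- add a sensitivity analysis of the group-by-time effect in pairs below the top at premeasurement, noting that it has fewer pairs and that they can still reach the cap afterwards;
- if the share at the top is material, state that a null on this item is not evidence of no effect on communication.

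This needs no new data, only a short table and one extra model.

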### Statistical Analysis

We will analyze relational quality and closeness (RQ1) with analysis of variance (ANOVA), with group (control, intervention) as between-subject factor and time (pre- and postmeasurement) as within-subject factor. We will compute the main effect for time and the interaction between time and group. In addition, we will analyze the correlation between connectedness and closeness and the factors contributing to higher increases in relational quality, if any.

To determine a statistically significant difference in the relational investment score (RQ2) between control and intervention groups as a result of the intervention, we will perform an ANOVA with group (control, intervention) as between-subject factor and time (pre- and postmeasurement) as within-subject factor. We will compute the main effect for time and the interaction between time and group. In addition, we will explore the factors contributing to higher increases in relational investment, if any.

To determine a statistically significant difference in the conversational resources score (RQ3) between control and intervention groups as a result of the intervention, we will perform an ANOVA with group (control, intervention) as between-subject factor and time (pre- and postmeasurement) as within-subject factor. We will compute the main effect for time and the interaction between time and group. In addition, we will explore the factors contributing to higher increases in conversational resources, if any. The resulting analysis will include an analysis of any unexpected or adverse effects of the intervention.

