## Methods

### Study Design

The study is designed as a randomized controlled trial (RCT) where both the intervention and control group consist of grandparent-grandchildren pairs. In the intervention group, we collect a set of pictures and short stories about the grandparents and share them with the grandchildren’s social network account, one at a time, at regular intervals across a period of 2 months. In the control group, there is no sharing or collecting pictures as the goal is to account for alternative effects.

Figure 1 shows the diagram of the study flow. Restricted randomization will be performed by stratifying gender, initial closeness level of the grandchildren, and age group of the grandparents. This paper reports on a version of the protocol accepted by the Research Ethics Committee at Mongolian National University of Medical Sciences in December 2017 (No. 2017/3-05).

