## Results

### Pilot

In order to validate the protocol and refine the entire intervention process by collecting actionable recommendations for how to execute the various phases, we conducted a pretest pilot from January to April 2018 among 6 pairs of participants (6 grandparents and 6 grandchildren). The validation of the protocol was focused on the process, instruments, and technological setup. We continued the study after the validation, and 59 pairs of participants (59 grandparents and 59 grandchildren) were recruited. Data collection was completed in November 2019.

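### The pre/post group-by-time ANOVA planned for RQ1 to RQ3 is valid under randomisation but uses the collected baseline inefficiently; baseline-adjusted ANCOVA would estimate the same effect more precisely

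*Protocol article*

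**What the plan says.** The Statistical Analysis section of the protocol article sets the same model for relational quality (RQ1), relational investment (RQ2) and conversational resources (RQ3): an ANOVA "with group (control, intervention) as between-subject factor and time (pre- and postmeasurement) as within-subject factor". In each case it adds: "We will compute the main effect for time and the interaction between time and group". It names neither a baseline covariate nor a stratification factor.

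A baseline exists for every outcome. Under Premeasurement, the grandchildren "complete the premeasurement questionnaire, which includes all instruments described in the Outcome Measures section". Under Postmeasurement, two months later, "The same questionnaires provided in the premeasurement session will be used".

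The Study Design section states: "Restricted randomization will be performed by stratifying gender, initial closeness level of the grandchildren, and age group of the grandparents". On size, the Participants section says "The aim is to recruit 60 grandparent-grandchild pairs, which will be split evenly into intervention and control conditions", and explains that "The sample size is limited by the specific focus of the intervention and the availability of participants complying with the criteria". The Pilot section reports that "59 pairs of participants (59 grandparents and 59 grandchildren) were recruited" and that data collection ended in November 2019.

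**The concern.** Of the two effects to be computed, only the interaction compares the randomised arms. With one pre and one post measurement it reduces to an unadjusted comparison of mean change. That comparison subtracts the whole baseline score from each participant's post score, whatever the actual relation between the two. If the relation is weaker than one-for-one, part of the baseline noise is carried into the treatment comparison.

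This matters more than usual here because the sample was set by availability and not by a power calculation, and recruitment is over. The analysis model is one of the few remaining ways to gain precision. The time main effect is a separate difficulty: it averages change over both arms, so it can be large when the intervention does nothing.

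**Working it through.** **Inputs from the article.** Two arms, two time points, 60 pairs split evenly, so 60/2 = 30 per arm. Every instrument is measured before and after. There is no stated power figure to reproduce.

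**Assumptions, because the article gives no values.** Two-sided alpha 0.05; a true effect of 0.6 SD of the post score; equal pre and post SDs (set to 1); within-arm pre-post correlation rho from 0.3 to 0.9.

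**Step 1: the interaction is a change-score t-test.** In a simulated data set with 30 per arm, the split-plot interaction F was 7.3665, and the squared two-sample t on change was 7.3665.

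**Step 2: error variances.**

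- Change score: 1 + 1 − 2·rho = 2(1 − rho).
- ANCOVA: 1 − rho².
- Ratio: (1 − rho)(1 + rho) / [2(1 − rho)] = (1 + rho)/2.

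The ratio is below 1 for every rho below 1. The price of ANCOVA with the baseline alone is one degree of freedom.

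**Step 3: power.** Noncentral t with noncentrality (0.6/s)·√(30/2), where s is the square root of the variance in step 2; 58 degrees of freedom for change and 57 for ANCOVA. At rho 0.5, for example, change has s = √1.00 = 1 and noncentrality 0.6 × 3.873 = 2.32, giving 63%. ANCOVA has s = √0.75 = 0.866 and noncentrality 2.68, giving 75%.

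| rho | variance, change | variance, ANCOVA | ratio | power, interaction | power, ANCOVA | pairs the interaction needs to match ANCOVA with 60 |
|---|---|---|---|---|---|---|
| 0.3 | 1.40 | 0.91 | 0.65 | 49% | 67% | 60/0.65 = 92 |
| 0.5 | 1.00 | 0.75 | 0.75 | 63% | 75% | 60/0.75 = 80 |
| 0.7 | 0.60 | 0.51 | 0.85 | 84% | 89% | 60/0.85 = 71 |
| 0.8 | 0.40 | 0.36 | 0.90 | 95% | 97% | 60/0.90 = 67 |
| 0.9 | 0.20 | 0.19 | 0.95 | 99.9% | 99.9% | 60/0.95 = 63 |

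At rho 0.5 the effect detectable with 80% power is 0.74 SD for the interaction and 0.64 SD for ANCOVA.

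**Step 4: bias.** In 6,000 simulated randomised trials with a true effect of 0.50 SD, both methods averaged 0.50. Their estimates within a single trial differed by 0.10 SD on average at rho 0.5 and by 0.06 SD at rho 0.7.

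**Step 5: does stratifying on initial closeness close the gap?** Randomisation was simulated within halves of the baseline score, with a 0.5 SD effect. Power was 48% for the interaction and 59% for ANCOVA at rho 0.5, and 70% vs 75% at rho 0.7. Stratification does limit imbalance: at rho 0.5 the SD of the change-score estimate fell from 0.255 to 0.235. The planned test gets no credit for this, because stratification is not in its error term.

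**Step 6: groups that are not randomised.** With a baseline difference D between groups, the ANCOVA estimate minus the change-score estimate is (1 − rho)·D. For D = 0.5 SD and rho = 0.5 this is 0.25 SD, so the two methods no longer aim at the same quantity.

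**The case against.** The strongest reply is that nothing in the planned analysis is incorrect. Under randomisation the interaction test is valid and unbiased, and it answers a question that is worded in terms of increase. That stands: this is a loss of efficiency, not an error.

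A reader might go further and infer that the plan throws the baseline away. It does not. A change score uses the baseline with a coefficient of 1. At rho 0.7 and a 0.6 SD effect it has 84% power, against 63% for the post score alone. The two tie at rho 0.5, and the change score does worse than ignoring baseline only below that.

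A reader might also take it as known that these scales have a slope well below 1. The article gives no reliability, SD or pre-post correlation, and the retest interval is only two months. A high correlation, with little to gain, cannot be excluded.

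Nor do the two methods give the same answer in any one trial. They agree in expectation, and only under randomisation. The Alternative Study Designs section allows a quasi-experimental fallback, by amendment, where that agreement fails.

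Stratification on initial closeness weakens the argument from chance imbalance for the closeness outcomes. It does not recover the lost power (step 5), and the RQ2 and RQ3 baselines are not stratification factors.

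**Conclusion.** The point holds as a precision improvement that should be made. For RQ1 to RQ3 the planned test of the intervention is a change-score t-test. Under randomisation ANCOVA targets the same effect with variance (1+rho)/2 as large, given equal pre and post SDs. The algebra is certain; the size of the benefit is not. Under the stated assumptions the gain is about 18 percentage points of power at rho 0.3, 12 at rho 0.5, 5 at rho 0.7, 2 at rho 0.8 and none at rho 0.9. Nowhere in that range is ANCOVA materially worse. The conclusion depends on the randomised design having been kept.

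**What to change.** - **Scale scores in RQ1 to RQ3, randomised design.** Fit the post score on group, the same instrument's pre score and the stratification factors from the Study Design section (gender, initial closeness, grandparent age group). Report the adjusted group difference with its 95% CI as the treatment effect.
- **Time main effect.** Do not use it as evidence that the intervention worked.
- **Communication frequency.** This is a single question with ordered response categories. Analyse it with a suitable ordinal model adjusted for its own baseline, not with linear ANCOVA.
- **Timing.** Data collection has ended, so record the change, with a date, before outcomes are compared by arm. If they have already been compared, report ANCOVA beside the planned ANOVA and say so.
- **Quasi-experimental fallback.** If it was used, the two analyses target different quantities, and the choice between them needs its own justification.

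The cost is revised analysis text, a documented amendment and a few degrees of freedom for the covariates. No new data are needed.
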